#### Criteria for discontinuation or modification of study intervention

2.4.5

No dose modification of the allocated intervention will be performed as the study medication is an MFDS-approved marketed drug. However, the allocated intervention may be discontinued, and the participant may be withdrawn from the trial prematurely in the event of serious adverse events, or if continuation of the trial is considered inappropriate based on clinical judgment during the study.

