#### Concomitant treatments

2.4.7

Participants currently taking herbal medicines or botanical preparations other than the study medication will not be eligible to participate in this study. In addition, participants may be withdrawn from the clinical trial if they take medications or other substances that may affect the evaluation of study outcomes during the study or follow-up period without the instruction or approval of the investigator.

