### Data collection and management

2.8

Assessments are scheduled at baseline (T1), mid-intervention (two weeks; T2), post-intervention (four weeks; T3), and follow-up (eight weeks; T4). Assessments include self-report ratings and heart rate variability (HRV) test. **Table 2** summarizes the assessment time points.

**Table 2 T2:** Study assessment points.

Assessments	Screening	T1	T2	T3	T4
SCID-HB	○				
CEAQ-s	○				
Blood test (Liver and Kidney Function Tests)	○			○	
Blood test (Thyroid Function Tests)	○				
Urine Test (u-HCG)	○				
Demographic Information	○				
HCT		○	○	○	○
STAXI-K		○	○	○	○
K-BDI, BAI		○		○	○
K-DERS		○	○	○	○
HRV		○		○	○
Adverse Events			○	○	○
Concomitant Medications	○		○	○	○
Medication Adherence			○	○	

T1, baseline; T2, mid-intervention; T3, post-intervention; T4, follow-up; SCID-HB, Structured Clinical Interview for Hwabyung; CEAQ-s, the Core Seven-Emotions Inventory Short Form; HCT, Hwabyung Comprehensive Test; STAXI-K, State-Trait Anger Expression Inventory-Korean Version; K-BDI, State–Trait Anger Expression Inventory-Korean Version; BAI, Beck Anxiety Inventory; K-DERS, Difficulties in Emotion Regulation Scale–Korean version; HRV test, Heart rate variability test.

To minimize participant dropout, sufficient information regarding the study schedule, assessment time points, and participant responsibilities will be provided at the start of the study. Reminder text messages will be sent prior to each assessment to notify participants of upcoming visits and survey schedules. Upon completion of the study, the participants will receive compensation that has been approved in advance.

If the participants withdraw from the study, no further assessments will be conducted. Data will be analyzed according to the intention-to-treat principle using linear mixed models, which account for missing data without explicit imputation. The reasons for discontinuation (e.g., personal circumstances, poor adherence, or adverse events) will be documented and recorded.

The research staff responsible for administering the questionnaire assessments and heart rate variability (HRV) measurements will remain blinded and will provide participants with procedural instructions that do not influence their responses. To improve data quality, missing items and abnormal responses will be checked when questionnaires are collected. In addition, key outcome variables will be double-checked when transferring participant data into an electronic case report form (eCRF).

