### Adverse events

2.12

Adverse events will be assessed after each session of MQT-SH. The results section will describe the type, frequency, and severity of the adverse events. Severity will be assessed according to three grades (mild, moderate, or severe). Mild is defined as adverse reactions that does not interfere with activities of daily living. Moderate is defined as an adverse reaction that interferes with daily life but is not dangerous. Severe is defined as an adverse reaction that is severe and interferes with basic daily activities (e.g., eating and changing clothes).

In addition, blood tests will be performed to evaluate liver and renal function. After venous blood collection, the serum or plasma will be separated, and the following parameters will be quantitatively analyzed: liver function test parameters (aspartate aminotransferase [AST], alanine aminotransferase [ALT], total bilirubin, direct bilirubin, alkaline phosphatase [ALP], and gamma-glutamyl transferase [GGT]) and renal function test parameters (blood urea nitrogen [BUN] and creatinine).

All laboratory analyses will be conducted at the Department of Laboratory Medicine at the study site using standardized automated equipment and established protocols. The results will be reported with reference ranges and used to assess the presence of hepatic or renal dysfunction.

Approximately 10 mL of whole blood will be collected at the time of testing, and the specimens will be discarded immediately after confirmation of the results and completion of the screening procedures.

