### Statistical analyses

2.13

The primary outcome is the symptom subscale of the HCT, with higher scores indicating greater symptom severity. Treatment efficacy will be evaluated based on the changes from baseline to Week 4.

Between-group differences will be analyzed using a linear mixed model (LMM). Fixed effects will include group (intervention vs. control), time (baseline, Week 4, and Week 8), and the group × time interaction, with the subject included as a random intercept. The LMM was selected because it appropriately accounts for within-subject correlation in repeated-measures data and allows the inclusion of participants with incomplete data under the maximum likelihood estimation framework, thereby reducing potential bias compared to complete-case analysis.

All efficacy analyses will be conducted according to the intention-to-treat (ITT) principle, including all randomized participants. Missing data will be handled under the assumption of missing at random (MAR) using maximum likelihood estimation within the LMM framework. In this study, reasons for dropout and the occurrence of adverse events will be collected whenever possible, and the MAR assumption was considered appropriate because missingness may be associated with observable factors such as previous measurements, treatment response, and adverse events. In addition, a per-protocol (PP) analysis reflecting adherence and major protocol violations will be performed to evaluate the consistency of the results.

The primary analysis will test the significance of the group × time interaction. A pre-specified contrast will be used to estimate the between-group difference in the mean change at Week 4. A decrease in score represents clinical improvement; therefore, a negative between-group difference in change (Δ intervention − Δ control) that is statistically significant will be interpreted as evidence of treatment efficacy.

Secondary outcomes (anger, depression, anxiety, HRV, and neurotic symptoms) will be analyzed using the same LMM framework. Variables without intermediate measurements, such as depression, anxiety, and HRV, can also be analyzed with LMM; in these cases, random slopes will be omitted and only random intercepts will be included. Contrasts can be specified to examine between-group differences at each time point. To control for multiplicity across secondary endpoints, the p-values will be adjusted using the Holm procedure.

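### Assessments end when a participant withdraws, and nothing provides for stopping study product while staying in follow-up, so the Week 4 analysis is intention-to-treat in name but lacks the follow-up

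*Protocol article*

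**What the plan says.** Four sections of the protocol article bear on this point.

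- **Section 2.8 (Data collection and management)** sets the follow-up rule: "If the participants withdraw from the study, no further assessments will be conducted". The same paragraph promises an intention-to-treat analysis by linear mixed model. It adds: "The reasons for discontinuation (e.g., personal circumstances, poor adherence, or adverse events) will be documented and recorded".
- **Section 2.4.5 (Criteria for discontinuation or modification)** says that "the allocated intervention may be discontinued, and the participant may be withdrawn from the trial prematurely in the event of serious adverse events", or where clinical judgment finds continuation inappropriate.
- **Section 2.4.7 (Concomitant treatments)** says that "participants may be withdrawn from the clinical trial if they take medications or other substances that may affect the evaluation of study outcomes" without the investigator's approval. This covers both the treatment and the follow-up period.
- **Section 2.13 (Statistical analyses)** says: "All efficacy analyses will be conducted according to the intention-to-treat (ITT) principle, including all randomized participants". It continues: "Missing data will be handled under the assumption of missing at random (MAR) using maximum likelihood estimation within the LMM framework". The model has fixed effects for group, time (baseline, Week 4, Week 8) and their interaction, plus a random intercept.

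On safety, section 2.12 says: "In addition, blood tests will be performed to evaluate liver and renal function". Table 2 schedules those tests at screening and T3 only. It schedules adverse-event assessment at T2, T3 and T4.

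The article describes neither a participant who stops study product but keeps attending, nor an early-termination visit.

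**The concern.** An intention-to-treat effect compares the arms as randomized, whatever happens to treatment afterwards. It needs outcomes from people who stop treatment or take something else, as well as their names in the analysis set. Here the reasons for which the investigator may withdraw someone arise after randomization, can differ between arms, and can be related to outcome. Once they lead to withdrawal, the stated rule ends measurement.

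The Week 4 contrast then depends on an assumption that the collected data cannot check. A later analysis plan can change a model or add a sensitivity analysis, but it cannot recover values that were never collected. Section 2.5 calls the trial confirmatory, and section 3.1 says that enrolment has begun, so the gap widens with each withdrawal.

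Safety is also a stated aim. A participant withdrawn before T3, possibly because of a serious adverse event, would have no scheduled post-dose laboratory result. On a plain reading, scheduled adverse-event assessment would stop as well.

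**Working it through.** **1. The plan's own sample size (section 2.5).** Inputs: d = 0.60, two-sided alpha 0.05, power 80%, dropout 15%.

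- n per arm = 2(1.960 + 0.842)² / 0.60² = 43.6, rounded up to 44; total 88.
- 88 / 0.85 = 103.5, rounded up to 104, or 52 per arm.

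Both figures reproduce. (The t distribution gives 44.6, or 45 per arm, and 79.5% power at 44; the difference is immaterial.) The sample size is not at fault.

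**2. How many participants are affected.** 0.15 × 104 = 15.6, about 16 in all; 0.15 × 52 = 7.8, about 8 per arm. The protocol does not say how many of these would leave before Week 4.

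**3. What an early leaver contributes to the primary model.** Section 2.13 lists time as baseline, Week 4 and Week 8. Table 2 measures the Hwabyung Comprehensive Test (HCT) at T2 too, but Week 2 is not in the stated model. As written, someone leaving before T3 contributes a baseline score only. A remark later in section 2.13 about variables without intermediate measurements may mean that Week 2 is intended for the others. If so, someone leaving between T2 and T3 contributes two scores, but still nothing after leaving.

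**4. What the missing-at-random assumption conditions on.** Section 2.13 justifies the assumption by saying that missingness may depend on previous measurements, treatment response and adverse events. The stated model contains group, time, their interaction and a subject intercept. It has no term for adverse events, adherence or concomitant medication, so the likelihood does not condition on them. The Week 4 contrast is informed almost entirely by those still attending.

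**5. Illustration of size.** Assumptions not in the protocol: a fraction p of the active arm leaves before Week 4; leavers lose a fraction L of the benefit; the standard deviation is unchanged; the model estimate stays at 0.60. Then

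all-randomized effect = 0.60 × (1 − pL), and overstatement = 1 / (1 − pL) − 1.

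| p | L | Effect d | Overstatement |
|---|---|---|---|
| 15% | 0 | 0.60 | 0% |
| 7.5% | 0.5 | 0.5775 | about 4% |
| 15% | 0.5 | 0.555 | about 8% |
| 7.5% | 1 | 0.555 | about 8% |
| 15% | 1 | 0.51 | about 18% |

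Power for the all-randomized effect when all benefit is lost (L = 1), with all 52 per arm measured (two-sided t-test, alpha 0.05):

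| p | Effect d | Power |
|---|---|---|
| 5% | 0.57 | 82% |
| 10% | 0.54 | 78% |
| 15% | 0.51 | 73% |
| 20% | 0.48 | 68% |
| 25% | 0.45 | 62% |

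**6. Laboratory schedule.** Liver and kidney tests fall at screening (before dosing) and T3. Leaving before T3 means no scheduled post-dose value. Leaving between T3 and T4 means that the T3 value exists.

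**The case against.** The best defence is that the stated analysis is sound as far as it goes, and that several stronger readings do not follow from the text.

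- **A reader might infer that withdrawn participants are excluded from the analysis.** They are not. Section 2.13 includes everyone randomized, and data recorded before withdrawal stay in the model. What is missing is their later outcomes.
- **A reader might infer that everyone who stops product is lost.** Sections 2.4.5 and 2.4.7 say that participants *may* be withdrawn, and section 2.4.5 names stopping the intervention and leaving the trial as two acts. Section 2.8 speaks of participants who withdraw, which could mean only those who choose to leave. The text is permissive and unclear; it is not a fixed rule that stopping product ends follow-up. Even so, no separate follow-up rule is given for those the investigator withdraws, so a plain reading applies the stop to them as well.
- **A reader might call the result the effect had everyone continued treatment.** That goes too far. Participants who miss doses but attend remain in the analysis. The estimate is closer to the effect had nobody left the study.
- **A reader might take 18% as the expected bias.** It is the top of the illustrated range at 15%. It needs all 15% to leave before Week 4 and every active-arm leaver to lose all benefit. Section 2.5 does not time the dropout, and personal circumstances, one of the listed reasons, need not relate to outcome.
- **A reader might infer that no early leaver has safety laboratory data, or that leavers are the likeliest to have abnormal values.** The gap concerns scheduled tests in those leaving before T3. Unscheduled tests are not ruled out, and nothing in the article links withdrawal to laboratory abnormality.

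It is also fair that a condensed article may leave sensitivity analyses for missing data to a plan not shown, so their absence is no finding here. That defence does not reach the follow-up rule, which the article states outright.

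**Conclusion.** The point holds as a data-collection defect. Section 2.8 ends assessments on withdrawal, sections 2.4.5 and 2.4.7 permit withdrawal for reasons that can relate to outcome, and nothing keeps such participants in follow-up. The analysis set is nominally intention-to-treat, but the Week 4 estimate does not rest on follow-up regardless of treatment discontinuation. For those who leave, it rests on a missing-at-random assumption in a model without the factors cited to support that assumption.

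The direction and size of any bias cannot be known from the documents. At the planned 15%, the illustration runs from none to about 18%, subject to the assumptions set out with it. The planned data could not show where in that range the trial lies. The safety consequence is narrower but certain: there is no scheduled post-dose liver or kidney result for anyone who leaves before T3.

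**What to change.** Reconcile sections 2.4.5, 2.4.7, 2.8 and 2.13 so that stopping study product, or being taken off it, is distinct from withdrawing consent. No clinical rule on when treatment stops needs to change.

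- Unless consent is withdrawn, collect the HCT, the other self-report outcomes and adverse events at the remaining scheduled visits, remotely if needed.
- Obtain the liver and kidney panel already planned for T3 at T3 or at the participant's last visit.
- State that these data enter the intention-to-treat analysis.

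The cost is a short amendment with ethics approval and a few extra contacts for at most about 16 participants. The primary instrument is a self-report form of 13 + 5 + 21 = 39 items, so remote collection is inexpensive. At best, measuring all 104 rather than 88 would cut the standard error by 1 − √(88/104), about 8%. That is an upper bound, because those who withdraw consent will still be missing. Since enrolment has started, the change should be made promptly.

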### Monitoring

2.9

Because this study is an investigator-initiated clinical trial, only minimal monitoring will be conducted owing to practical resource constraints. The chair of the data monitoring committee will be the principal investigator who will oversee whether the monitoring process is conducted appropriately and will make the final decision regarding study termination. Another committee member will be a researcher responsible for monitoring the management and dispensing of the study medication. This researcher is aware of the purpose and design of the clinical trial but is not involved in the actual conduct of the study. Monitoring related to study medication management will be conducted through pharmacy visits every two months.

Owing to limited research resources, separate monitoring of the integrity of the source documents, case report forms (CRFs), and electronic case report forms (eCRFs) will not be performed. Instead, data consistency and entry errors will be minimized through field-level input validation (edit checks) and the automatic query generation functions for potential errors provided through the iCLICK system.

### Primary outcomes

2.10

#### HCT

2.10.1

The HCT (16) will be used to assess Hwabyung-related symptoms and psychological characteristics. This test comprises 13 items on Hwabyung symptoms, 5 items on the incident questionnaire, and 21 items on Hwabyung psychological characteristics. Hwabyung symptoms and psychological characteristics will be used to interpret scores. This test is a self-reported 5-point Likert scale. The total score ranges from 0 to 52 for Hwabyung symptoms, and from 0 to 84 for Hwabyung psychological characteristics. Higher scores indicate more severe Hwabyung symptoms and vulnerability. In a previous study (16), the Cronbach’s alpha for the HCT was 0.89 for Hwabyung symptoms and 0.95 for Hwabyung psychological characteristics.

In this study, the symptom subscale of the instrument will be designated as the primary outcome variable, and the psychological characteristics subscale will be treated as the secondary outcome variable.

### Secondary outcomes

2.11

#### State-trait anger expression inventory

2.11.1

The Korean Adaptation of the State-Trait Anger Expression Inventory (22) will be used to assess anger experiences and expression. This scale consists of 10 items on state anger, 10 items on trait anger, and 24 items on anger expression. This is a self-reported 4-point Likert scale. The total score ranges from 10 to 40 for state anger, 10 to 40 for trait anger, and 24 to 96 for anger expression. Anger expression comprises three factors: anger-out, anger-in, and anger control. Anger control is considered a functional expression of anger and will be reverse calculated. A higher score indicates experiencing and expressing more anger. In a previous study (22), Cronbach’s alpha was.90 for state anger, 0.75 for trait anger, 0.70 for anger-out, 0.66 for anger-in and, 0.79 for anger-control.

#### Beck depression inventory

2.11.2

The Korean version of the Beck Depression Inventory (K-BDI) originally developed by Beck (23) and subsequently translated and validated for use in Korea by Rhee et al. (24) was used. The K-BDI is a self-report instrument designed to assess depressive symptoms and consists of 21 items rated on a 4-point scale (0–3). Higher total scores indicate greater severity of depressive symptoms. In a validation study (24), the internal consistency reliability was 0.85.

#### Beck anxiety inventory

2.11.3

The Beck Anxiety Inventory (BAI), originally developed by Beck et al. (25), and subsequently adapted to Korean by Yook and Kim (26), will be used. The BAI is a self-report instrument designed to assess anxiety symptoms and consists of 21 items rated on a 4-point scale (0–3). Higher total scores indicate greater severity of anxiety symptoms. In a validation study (26), the internal consistency reliability was 0.91.

#### Difficulties in emotion regulation scale

2.11.4

To assess neurotic symptoms, the Korean version of the Difficulties in Emotion Regulation Scale (K-DERS), originally developed by Gratz and Roemer (27) and subsequently translated and validated in Korean by Cho (28), will be used. Neurotic symptoms are closely associated with emotional sensitivity, hyperarousal, and impulsive responses, all of which reflect difficulties in emotional regulation. The DERS is a validated multidimensional instrument designed to assess these domains. Therefore, it is considered an appropriate measure to indirectly evaluate the characteristics of neurotic symptoms.

The scale consists of 35 items rated on a 5-point Likert scale (1–5). Higher total scores indicated greater difficulty in emotion regulation. In a validation study (28), the internal consistency reliability was reported as 0.92.

#### Heart rate variability test

2.11.5

The HRV test is used to assess autonomic nervous system regulation. It consists of time-domain and frequency-domain analyses.

In the time-domain analysis, the following parameters will be measured: mean heart rate (MHR; average heart rate), standard deviation of NN intervals (SDNN; overall variability of heartbeats over the recording period), root mean square of successive differences (RMSSD; short-term variability in heart rate), and Physical Stress Index (PSI; an indicator of physical stress level).

In the frequency domain analysis, the following parameters will be assessed: total power (TP; overall autonomic nervous system activity), very low frequency (VLF; an additional sympathetic index), low frequency (LF; sympathetic activity index), high frequency (HF; parasympathetic activity index), LF norm, HF norm, and LF/HF ratio.

### Adverse events

2.12

Adverse events will be assessed after each session of MQT-SH. The results section will describe the type, frequency, and severity of the adverse events. Severity will be assessed according to three grades (mild, moderate, or severe). Mild is defined as adverse reactions that does not interfere with activities of daily living. Moderate is defined as an adverse reaction that interferes with daily life but is not dangerous. Severe is defined as an adverse reaction that is severe and interferes with basic daily activities (e.g., eating and changing clothes).

In addition, blood tests will be performed to evaluate liver and renal function. After venous blood collection, the serum or plasma will be separated, and the following parameters will be quantitatively analyzed: liver function test parameters (aspartate aminotransferase [AST], alanine aminotransferase [ALT], total bilirubin, direct bilirubin, alkaline phosphatase [ALP], and gamma-glutamyl transferase [GGT]) and renal function test parameters (blood urea nitrogen [BUN] and creatinine).

All laboratory analyses will be conducted at the Department of Laboratory Medicine at the study site using standardized automated equipment and established protocols. The results will be reported with reference ranges and used to assess the presence of hepatic or renal dysfunction.

Approximately 10 mL of whole blood will be collected at the time of testing, and the specimens will be discarded immediately after confirmation of the results and completion of the screening procedures.

